### Health outcomes

Three health effects will be considered for different CEAs to bring different perspectives when decision-making. The primary health effect considered will be the number of new operative interventions per child after the baseline assessment. Other endpoints were set as secondary health effects: the time to the new operative interventions (survival), the percentage of children who did not need new operative interventions, and the relevant change in the Oral Health-Related Quality of Life (OHRQoL) scores (Table 2).

**Table 2 Tab2:**
[figure not shown]
Summary of health outcomes (health effects) used in economic evaluations

*95%CI** bootstrap-adjusted confidence interval at 95%

For the first health outcomes (related to new operative interventions), we will assess the children for 24 months, following them each 6 months. The cumulative result will be accumulated for 24 months when computing the number of events (new interventions) and the time to an event during this period. The restorations will be evaluated by an examiner ([name]), blinded to the diagnostic strategy. At this assessment, surfaces were scored according to the restoration integrity and occurrence of caries, determining the need (or not) of repair, replacement, or other possible new interventions [22, 23] (Table 2). At this stage, the idea was to use an external assessor using a different approach (from those interventions under comparison and randomized) not to bias the outcome assessment. Based on this assessment, new interventions (events) will be considered when any need for restoration repair or replacement is identified, any presence of secondary caries lesion exposing dentin is detected, any need for extension of the existing restoration or endodontic treatment is required (due to caries or tooth fracture), and/or any episode of pain is reported (Table 2).

The OHRQoL will be assessed using the Brazilian version of the Early Childhood Health Impact Scale (B-ECOHIS) [24]. This questionnaire is answered by parents as a proxy of the child’s OHRQoL and is a valid measure for children [25]. Although the ECOHIS has been proposed for pre-school children [26], it was chosen to measure effectiveness in the entire sample, comprising children from 3 to 9 years old. The questionnaire was answered in the baseline and will be answered at 24-month follow-up completion. The difference between the ECOHIS final and baseline scores will be calculated. The change in ECOHIS scores will be classified according to the minimal important difference calculated [25].

For CUA, the effect will be the gain in tooth-related quality-adjusted life years (QALYs). To estimate tooth-related QALYs, we will use the Standard Gamble (SG) approach to calculate weights (utility scores) based on the patient’s parent’s preferences regarding health states related to dental caries. For that, we anchored the weighs in tooth loss (the worst scenario). The parent preference will be used as a proxy measure for the child’s preference regarding different health statuses. More details about the Standard Gamble experiment may be found in the next section.

### Standard gamble

We will conduct an SG experiment to measure different oral health states’ preferences related to dental caries in primary teeth. As parents’ answers will be considered a proxy measurement, a representative sample of those parents seeking dental treatment in a reference center will be selected. A minimum sample size of 50 parents was calculated to permit an absolute difference of 0.05 units and guarantee the power of 80% and a significance level of 5%. To compensate for possible non-normal distribution and possible non-response or lost participants, we added up, respectively, 10% and 20% to this calculated sample, totalizing 63 participants to be recruited.

The recruited sample will be stratified by the child’s caries experience and opportunity for dental treatment (children firstly seeking the treatment vs those already enrolled in treatment) to contribute to the sample representativeness. Part of this sample will be selected among children’s parents from the main clinical trial (CARDEC-3). The other will be recruited among parents whose children are seeking treatment in the school’s dental clinics. Adults will be asked about their preference between two courses of action resulting in different outcomes regarding their child’s oral condition.

The health states will be illustrated on cards, and the SG will be conducted using a chance board. The health states considered are (1) a primary molar with dentin caries lesion; (2) a restored primary molar; (3) a restored primary molar needing repair/replacement. Children’s parents will choose between alternatives A and B. Alternative A offers a probability “p” of achieving the best possible health state, which is a sound tooth that will last like that until it exfoliates. Then, a probability “1 − *p*” of having the worst possible condition is assumed (early tooth loss) (Fig. 1). Alternative B will be a particular health state of a restored primary molar. The probability “*p*” will be changed in the chance board until the parent is indifferent to the two options [27]. This probability will be considered the parent’s preference (utility weight) for their child’s health state (utility value). We will then calculate the tooth-related QALYs, also considering the time for which the child presented such a state. The same experiment with the other health states will be conducted, as demonstrated in Fig. 1.

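### The standard-gamble recruitment target of 63 parents does not follow from adding both stated allowances (10% and 20%) to 50, which gives 65, 66 or 69

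*Protocol article*

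**What the plan says.** The Standard gamble section of the protocol article sizes the survey in two steps.

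- **Base size:** "A minimum sample size of 50 parents was calculated to permit an absolute difference of 0.05 units", with 80% power and a 5% significance level.
- **Inflation:** the purpose is given as "To compensate for possible non-normal distribution and possible non-response or lost participants", and the amounts as "we added up, respectively, 10% and 20% to this calculated sample, totalizing 63 participants to be recruited".

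Read with the word for respective order, the 10% belongs to non-normality and the 20% to non-response or loss. Both are described as applied to the calculated sample, which is the 50. The article gives no inflation formula.

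The survey's utility weights are used for the tooth-related QALYs in the cost-utility analysis (Health outcomes) and as utility values in the Markov model (Modelling for primary tooth lifetime horizon).

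**The concern.** The base, both percentages and the total all stand in running prose, so a reader can check the sum directly, and it does not come out. The recruitment target is therefore wrong as described: either the total or the description of the allowances needs correcting.

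At stake is whether the survey has the reserve that the authors thought it needed. They considered non-normality of the utility scores worth an allowance, and the total does not show one. The Background also gives reproducibility and transparency as reasons for publishing the plan, and this target cannot be reproduced from its stated inputs.

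**Working it through.** **Inputs (all from the Standard gamble section):** base n = 50; difference 0.05; power 80%; significance level 5%; allowances 10% and 20%; stated total 63. The SD, the design and the sidedness of the test are not given in the article.

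**Step 1. Can 63 be reproduced?**

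With both allowances on 50:
- additive: 50 × (1 + 0.10 + 0.20) = 65
- compounded: 50 × 1.10 × 1.20 = 66
- 10% added, then 20% as a loss fraction: 50 × 1.10 / 0.80 = 68.75, so 69
- both as loss fractions in turn: 50 / 0.90 / 0.80 = 69.4, so 70
- both as one combined loss fraction: 50 / 0.70 = 71.4, so 72

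With one allowance only:
- 10% added: 50 × 1.10 = 55
- 20% added: 50 × 1.20 = 60
- 20% as a loss fraction: 50 / 0.80 = 62.5, so **63**

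Only the last line gives the stated total. Against 65, 66 and 69, the target is short by 2, 3 and 6 parents.

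**Step 2. What does 63 deliver?**

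Assume a one-sample or paired comparison, a two-sided 5% test and the normal approximation. Then 1.96 + 0.8416 = 2.8016, and the SD implied by n = 50 is 0.05 × √50 / 2.8016 = 0.126. This SD is back-solved, not stated, and depends on the assumed design; two groups of 25 would imply about 0.063. Power at an effective size n is

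Φ(2.8016 × √(n/50) − 1.96).

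- **20% lost, no cost from non-normality:** 63 × 0.80 = 50.4, power 80.3%.
- **20% lost and the full 10% also needed:** 50.4 / 1.10 = 45.8, power 76.5%.
- **Both allowances as compounded add-ons, fully needed:** 63 / (1.10 × 1.20) = 47.7, power 78.1%.
- **Both as summed add-ons, fully needed:** 63 / 1.30 = 48.5, power about 79%.

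**Step 3. Do the alternative targets hold 80% on the strictest of these measures (20% lost, then divided by 1.10)?**

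| Recruited | After 20% loss | Effective n | Power |
|---|---|---|---|
| 63 | 50.4 | 45.8 | 76.5% |
| 65 | 52.0 | 47.3 | 77.8% |
| 66 | 52.8 | 48.0 | 78.4% |
| 69 | 55.2 | 50.2 | 80.1% |

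So 65 and 66 agree with the sentence under an add-on formula, but only 69 keeps 80% if the 20% is a loss fraction and the 10% is fully used.

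**Step 4. Effect on precision.** The standard error of a mean utility scales with 1/√n. Recruiting 63 makes it larger by √(65/63) − 1 = 1.6% than with 65, by √(66/63) − 1 = 2.4% than with 66, and by √(69/63) − 1 = 4.7% than with 69.

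**The case against.** Three points can be made for the plan.

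**Power survives the expected loss.** A reader might infer from the failed sum that the survey misses its 80% power. The article does not support that. It attaches 80% to 50 parents, and 63 less the full 20% leaves 50.4. Power falls only if non-normality also costs the whole 10%, which the article lists as a possibility. This point stands, and it limits the finding to the 10% reserve.

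**The 10% may not have been left out.** A reader might also conclude from the match with 50/0.80 that the 10% was forgotten. That is an inference. If, for example, an uninflated 45 had been raised by 10% to 49.5, rounded to 50 and then divided by 0.80, the total would be 63 with both allowances included. That route conflicts with the statement that both percentages were added to the calculated sample, so the sentence would still need correction. It does show that the fault may lie in the description and not in the target, and the article cannot settle which.

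**The consequence is slight.** The utilities enter the cost-utility analysis and the Markov model as inputs, and the article describes no test on them through which a few points of power would change those results. The primary health effect is the number of new operative interventions per child. This also stands, and it sets the severity.

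The absence of a stated SD is not part of this point, because a condensed article may leave it to a fuller document.

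**Conclusion.** The point holds as an arithmetic and reporting inconsistency of minor severity. No way of applying both allowances to 50 gives 63; the shortfall is 2 parents (additive), 3 (compounded) or 6 (20% as a loss fraction). The total is consistent with the 20% allowance alone, but its derivation is not documented.

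The stated 80% power is kept after 20% loss. If the 10% reserve were fully needed as well, power would be about 76% to 78% on the loss-fraction and compounded readings, and about 79% on the summed one. These power figures rest on the assumed one-sample or paired two-sided design and the back-solved SD; the arithmetic mismatch needs no assumption. The effect is confined to an ancillary utility survey. The randomised comparison and the primary cost-effectiveness analysis are not touched.

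**What to change.** State the inflation formula in the Standard gamble section and make the figures agree with it, in one of two ways:

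- correct the target to the value that the formula gives: 65 (summed), 66 (compounded) or 69 (10% added, then divided by 0.80); or
- keep 63 and say that it covers the 20% non-response allowance only, with no separate reserve for non-normality.

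If 50 already includes the 10%, say so and give the uninflated figure.

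The cost is one corrected sentence and, if the target is raised, 2 to 6 more parent interviews. If recruitment to the survey is already closed, the second option costs nothing beyond the wording.

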### Analytical methods

The economic evaluations will be considered intention-to-treat analyses using data collected after 2 years, as previously described. In the case of missing data, we will investigate their nature and choose the most appropriate method to handle the missing data, e.g., multiple imputations. Imputations will consider health and economic outcomes and the possible relationship between them and other pertinent covariates. When new operative treatments have been performed externally to the research, the same strategy used for missing data will be used for cost estimation.

Cox regression model with shared frailty will be used to compare the need for a new intervention. The health effects listed above will be compared between groups using the most appropriate statistical test, depending on data distribution. Given the usual right-skewed distribution of cost data, we will use the bootstrapping quantile regression to compare the total costs of the diagnostic strategies [28]. Bootstrapping replications will be set at 1000, and a fixed seed will be determined. We will use the software Stata13 (StataCorp LP, Texas, USA) and set a 5% significance level for these analyses.

We will work with the difference between the strategies both regarding the inputs (∆costs: CARS costs − FDI costs) and outputs (∆effects: CARS effects − FDI effects) since the focus of this series of economic evaluations is the economic impact of using the minimally invasive strategy (based on CARS) instead of the conventional strategy (based on FDI criteria) for managing dental restorations. Bootstrap confidence intervals will be calculated for each parameter considering the costs, effects, incremental costs, and incremental effects [29].

Deterministic one-way sensitivity analysis will be conducted for CEAs and CUA to assess the quantitative relationship among estimates in parameters that could perform differently in a distinct scenario, such as costs, discount rate, and effects. In these analyses, we will also test the influence of different baseline conditions as covariates associated with the effects and costs [30], checking the possibility of extrapolating data from this single trial to a broader population. The results will be demonstrated in a tornado diagram.

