Additionally, a Bayesian approach will be used to explore uncertainties on the same parameters. By adopting this approach, we will describe the probabilities around the actual values obtained in this study [31–33]. The data distribution of costs and effects will be checked using XLSTAT Premium 2021.3.1 (Addinsoft, Paris, France), and, based on that distribution, Monte-Carlo simulations (× 10,000) will be generated to be plotted in a cost-effectiveness plane (CE plane). The proportion of points in each quadrant of the CE plane will be calculated, and the location of points will also be assessed visually. We will calculate the incremental net benefit using the following equation:

Incremental Net Benefit = Incremental Effect × Ceiling Ratio − Incremental Cost, being value 1 for a positive coefficient and 0 for a negative coefficient value. Thus, for the interpretation, if the difference is higher than zero (the value 1), it means that for one additional unit of effectiveness, the incremental cost is below the Ceiling Ratio (the maximum value that decision-makers are willing to pay). If the difference is less than zero (the value 0), the incremental cost of each additional unit of effectiveness is above the Ceiling Ratio [34]. Finally, acceptability curves will be plotted for each effect using the incremental net benefit framework and assuming different ceiling ratios to check the uncertainties around threshold points.

Subgroup analyses considering age (3 to 6 vs 7 to 10 years) and patients’ caries experience (≤ 3 vs > 3 restorations) will also be conducted.

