### Modelling for primary tooth lifetime horizon

We will construct a decision analytic modelling framework to extrapolate the findings considering a longer time horizon (the primary molar lifetime) (Supplemental File 3). As the base case, we will consider a child as those enrolled in the trial. Then, based on the mean age of children enrolled on the main trial, we will establish the number of cycles of the Markov model.

Probabilities and costs will be extracted from the main trial. If necessary, any additional reference value will be identified from the literature. The SG experiment will generate utility values. We will assume that probabilities will maintain the same at each cycle during the time horizon. The half-cycle correction will be used to account for the fact that events and transitions can occur at any point during the cycle, not necessarily at the start or end of each cycle.

We will adopt the same strategies adopted in the trial-based analyses for deterministic and probabilistic analyses using the model framework. The final interpretation of uncertainties will be considered for this longer time horizon. Data will be modelled and analyzed using a Markov simulation model. Tree Age Pro 2017 (TreeAge Software, Williamstown, MA, USA).

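### As described, the trial-based cost-utility analysis does not carry the sampling error of the standard-gamble weights into the QALY interval or the acceptability curve

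*Protocol article*

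**What the plan says.** All references are to the Protocol article.

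- **Weights (Standard gamble).** Three health states are valued by parents. On size: "A minimum sample size of 50 parents was calculated to permit an absolute difference of 0.05 units", with 80% power at a 5% significance level. Then: "we added up, respectively, 10% and 20% to this calculated sample, totalizing 63 participants to be recruited". On source: "Part of this sample will be selected among children’s parents from the main clinical trial (CARDEC-3"); the rest are parents seeking care for their children at the school's clinics.
- **QALYs (Standard gamble).** "We will then calculate the tooth-related QALYs, also considering the time for which the child presented such a state".
- **Intervals (Analytical methods).** "Bootstrap confidence intervals will be calculated for each parameter considering the costs, effects, incremental costs, and incremental effects", with 1000 replications set for the bootstrapping.
- **Probabilistic analysis (Analytical methods).** "The data distribution of costs and effects will be checked", and 10,000 Monte-Carlo values are generated from the resulting distribution. These values go to the cost-effectiveness plane; an acceptability curve for each effect is then built from incremental net benefit.
- **Lifetime model (Modelling for primary tooth lifetime horizon).** Utilities come from the standard-gamble experiment. On uncertainty: "We will adopt the same strategies adopted in the trial-based analyses for deterministic and probabilistic analyses using the model framework".

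No section says that the standard-gamble parents are resampled or that the weights are given a distribution. No section says that the weights are held at their point values either.

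**The concern.** A QALY difference here is a two-source estimate: time in state from the trial, and utility weights from a small preference study. Any child whose parent was not in that study must take a shared mean weight. Error in a shared weight moves every child's QALY together, so it leaves no trace in the spread of QALYs between children. Resampling children, or fitting a distribution to their QALYs, cannot recover it.

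At stake are the interval for incremental QALYs, the scatter on the cost-effectiveness plane, and the probability that CARS is cost-effective per tooth-related QALY. If the weight error is left out, that probability will usually lie further from 50% than the data justify.

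**Working it through.** **1. The plan's own sample size.** The 50 cannot be reproduced, because neither an SD nor a design is given. Working backwards, assuming a one-sample or paired comparison and a two-sided test:

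- SE = 0.05 / (1.960 + 0.842) = 0.05 / 2.802 = 0.0178
- SD = 0.0178 × √50 = 0.126

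With 63 parents and the same SD, SE = 0.126 / √63 = 0.0159. A two-group reading would imply an SD of 0.063 (25 per group) or 0.089 (50 per group). Adding 10% and 20% to 50 gives 65 (or 66 if compounded), whereas 63 equals 50 / 0.8 rounded up. That small discrepancy does not affect this point.

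**2. Effect on the QALY difference.** Simplify to two states with fixed total time. Let g be the utility gap between them and ΔT the between-arm difference in time spent in one of them, so that ΔQALY = g × ΔT. With independent estimates:

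Var(ΔQALY) = g²·Var(ΔT) + ΔT²·Var(g) + Var(g)·Var(ΔT)

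With the weights fixed, only the first term is counted. Writing CV = SE(g)/g and Z = ΔT/SE(ΔT), the ratio of the full SE to the fixed-weight SE is √(1 + CV²Z² + CV²). The first-order version drops the final CV².

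**3. Results at 50 parents, SD 0.126.** The values of g and Z are assumptions; the document gives neither.

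| Gap g | CV | First order, Z = 2 | Full, Z = 2 | Full, Z = 3 | Coverage of nominal 95% fixed-weight interval, Z = 2 |
|---|---|---|---|---|---|
| 0.05 | 0.36 | 1.23 | 1.28 | 1.51 | 84% |
| 0.10 | 0.18 | 1.06 | 1.08 | 1.15 | 93% |
| 0.20 | 0.09 | 1.02 | 1.02 | 1.04 | 94.5% |

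Worked line for g = 0.05, Z = 2: CV = 0.0178/0.05 = 0.357 and CV² = 0.127; √(1 + 4 × 0.127) = 1.23; √(1 + 4 × 0.127 + 0.127) = 1.28. Coverage comes from a simulation of 200,000 runs per setting.

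At Z = 0 the first-order ratio is 1, the full ratio is 1.06, 1.02 and 1.00 for the three gaps, and coverage stays at 95%. With 63 parents the full ratios at Z = 2 are 1.23, 1.06 and 1.02.

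**4. A larger SD (assumed 0.30, 50 parents, Z = 2).** SE(g) = 0.30 / √50 = 0.042. The full ratios are 2.15, 1.38 and 1.11 for gaps of 0.05, 0.10 and 0.20, with coverage of 64%, 80% and 92%.

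**5. Acceptability curve.** Incremental net benefit is λ·ΔQALY − ΔCost, where λ is the ceiling ratio. Omitting weight error removes about λ²·ΔT²·Var(g) from its variance. The loss therefore grows with λ, and its importance depends on the variance of the cost difference, which the document does not give. The direction can be stated; the shift in probability cannot.

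**The case against.** A reader might infer that the plan fixes the weights at their point values, that its cost-utility intervals are therefore too narrow, and that the lifetime model inherits the fault. The text does not support that much.

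- **No section says the weights are fixed.** The parameters listed for the one-way analysis are examples, the list covers the cost-utility analysis, and the probabilistic analysis is said to address the same parameters. This stands against a flat assertion. It does not close the gap: varying a QALY effect over an interval that already lacks weight error still leaves that error out, and the plan does say that the draws come from the distribution of costs and effects.
- **In the Markov model, utilities are inputs.** The modelling section promises a probabilistic analysis and excludes nothing, and Supplemental File 3 is not shown. This stands, and for that model only a request for confirmation is justified.
- **An article may leave coding detail elsewhere.** That is true in general. But this article is itself the health economic analysis plan, and it fixes the number of replications, the number of draws and the source of the draws. Which inputs are random belongs at the same level.
- **The samples overlap.** Some standard-gamble parents are trial parents, so the two sources are not fully independent. That qualifies the formula above but does not remove the sampling error.
- **The size rests on assumptions.** The paired design, the SD, the utility gap and the time difference are all assumed, and for well-separated states the effect is trivial. This stands.
- **The cost-utility analysis is not the primary evaluation.** The Health outcomes section makes the number of new operative interventions the primary effect. This limits the consequence.

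**Conclusion.** The point holds for the trial-based cost-utility analysis. Followed as described on per-child QALYs, the stated methods omit the sampling error of the standard-gamble weights. The direction is clear: the SE of the QALY difference is understated, and the acceptability curve is misstated, usually by being too steep.

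The magnitude cannot be settled from the document. Under the paired two-sided reading with a time difference of 2 SE, it runs from about 2% (gap 0.20) through 6–8% (gap 0.10) to 23–28% (gap 0.05). Small gaps are relevant because the preference study was itself sized on a difference of 0.05. A larger SD would raise these figures; a time difference near zero would make the omission immaterial.

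**What to change.** Add a sentence to the Analytical methods section stating that, in each bootstrap replicate and each Monte-Carlo draw for the cost-utility analysis:

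1. the standard-gamble parents are resampled as well, keeping each parent's three weights together;
2. the mean weights are recomputed;
3. QALYs are recalculated with the same redrawn weights in both arms.

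State how parents who also have a child in the trial are handled, so that the overlap is not left to chance. Add the weights to the tornado diagram, each varied over its 95% confidence interval. For the Markov model, confirm that utilities are given distributions in the probabilistic analysis.

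The cost is a little more code and one or two sentences of text, with no new data. The downside is somewhat wider cost-utility intervals. If the sponsor already intends this, the change only puts it on record.
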